### Demographics

Several background and socio-demographic variables will be collected at screening for informal carers and stroke survivors.

The collected variables for an informal carer: source of referral; age; gender; ethnic background; relationship status; relationship to stroke survivor; employment status; yearly household outcome; highest level of academic qualification; length of time caring; whether lives with the stroke survivor; provision of care before the stroke; receipt of support services in the home; hours of support services received in the home per week, and hours of caring per week.

The collected variables for a stroke survivor: age; gender; ethnic background; relationship status; employment status; date of first stroke; date of most recent stroke; type of first stroke (ischemic, hemorrhage, transient ischemic attack (TIA)); type of most recent stroke, (ischemic, hemorrhage, TIA) and whether the stroke survivor is aphasic.

### Data collection

Dependent upon participant preference, the researcher will collect data either over the telephone or face-to-face at screening, baseline, four months and six months post-randomization. The adapted CSRI will be collected via post due to the potential for unblinding as the measure includes information about the receipt of psychological treatment. A summary of outcomes collected at each time point can be seen in Table 
1.

**Table 1 T1:** Study clinical outcome measures by time point

**Outcome measure**	**Time point**
Demographics (informal carer)	Initial screen
Demographics (stroke survivor)	Initial screen
PHQ-9	Initial screen; four months post-randomization; six months post-randomization
GAD-7	Initial screen; four months post-randomization; six months post-randomization
CIS-R	Full screen; four months post-randomization; six months post-randomization
WASAS	Baseline; four months post-randomization; six months post-randomization
CBS	Baseline; four months post-randomization; six months post-randomization
BI	Baseline; four months post-randomization; six months post-randomization
FAI	Baseline; four months post-randomization; six months post-randomization
SF-36	Baseline; four months post-randomization; six months post-randomization
EQ-5D	Baseline; four months post-randomization; six months post-randomization
Health and public service use	Baseline; four months post-randomization; six months post-randomization

*BI*, Barthel activities of daily living index; *CBS*, Caregiver burden scale; *CIS-R*, Clinical interview schedule; *EQ-5D*, EuroQol-5D; *FAI*, Frenchay activities index; *GAD-7*, Generalized anxiety disorder 7-item scale; *PHQ-9*, Patient health questionnaire-9; *SF-36*, Short form (36) health survey; *WSAS*, Work and social adjustment scale.

### Acceptability of the intervention

#### Study objectives and design

We will conduct a sub study to examine the following question: what are participants’ views on the acceptability of CBTsh? Semi-structured interviews will be conducted with all participants randomized to receive CBTsh to examine the acceptability of the new intervention. Open-ended questions will be asked around participants’ impressions of supported CBTsh; the relevance and suitability of the intervention for carers and relatives of stroke survivors; receiving support; specific interventions used; perceived benefit and impact of the intervention; difficulties experienced using the intervention; continued use of self-help strategies; and recommendations for future development. The topic guide has been partially informed by a previous qualitative study investigating the acceptability of online-based CBTsh for depressed patients with multiple sclerosis
[29]. Non-attendees and poor attendees will also be asked about reasons for dropping out of the intervention and to consider what a more acceptable intervention may look like. Interviews will be semi-structured and conducted over the telephone. Interviews are anticipated to last between 45 and 90 minutes, however the duration may be shorter for those categorized as non-attendees and poor attendees.

### Sampling

All participants allocated to receive the intervention will be invited to participate. Dependent upon attendance of support sessions, participants will be categorized into one of the following: (i) non attendees, defined as not attending any sessions; (ii) poor attendees, defined as attending the assessment session and then terminating treatment before reaching a shared decision with the PWP to be discharged from treatment; or (iii) completers, defined as those who engage in treatment until a shared decision is made with the PWP to terminate treatment.

### Statistical analysis

#### Quantitative

Data analysis will mainly be descriptive and address the primary outcomes relating to the feasibility of conducting a future definite RCT. Participant flow will be summarized following the CONSORT diagram
[46]. Recruitment and attrition rates (both treatment and study dropouts) will be calculated, along with 95% confidence intervals. Protocol deviations, along with reasons and number of missing items on questionnaires will be reported. The mean and standard deviation for each outcome measurement will be reported at baseline, four, and six months. The mean and standard deviation will also be reported for the number, length, and frequency of support sessions required to bring about recovery.

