**Methods/Design:**

This study is a Phase II (feasibility) randomized controlled trial (RCT) following guidance in the MRC Complex Interventions Research Methods Framework. We will randomize a sample of depressed informal carers of stroke survivors to receive CBT self-help supported by mental health paraprofessionals, or treatment-as-usual. Consistent with the objectives of assessing the feasibility of trial design and procedures for a potential larger scale trial we will measure the following outcomes: a) feasibility of patient recruitment (recruitment and refusal rates); (b) feasibility and acceptability of data collection procedures; (c) levels of attrition; (d) likely intervention effect size; (e) variability in number, length and frequency of support sessions estimated to bring about recovery; and (f) acceptability of the intervention. Additionally, we will collect data on the diagnosis of depression, symptoms of depression and anxiety, functional impairment, carer burden, quality of life, and stroke survivor mobility skill, self-care and functional ability, measured at four and six months post-randomization.

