### Study aims and objectives

We will conduct a feasibility phase II RCT
[44,45] comparing a written CBTsh intervention for depressed informal carers of stroke survivors supported by paraprofessional mental health workers (Psychological Wellbeing Practitioners; PWPs) with treatment-as-usual (TAU). Outcomes will assess a number of methodological and procedural uncertainties that require investigation prior to designing and applying for funding for a Phase III trial. Therefore the following four questions will be addressedFor informal carers of stroke survivors receiving CBTsh in a fully powered phase III trial, what would be the estimates of likely recruitment and retention rate; estimates of the range of effect sizes; feasibility and acceptability of data collection methods and instruments; and acceptability and structure of the treatment procedures to participants?

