### Randomization and allocation concealment

We will randomly allocate eligible participants to one of the two study arms - supported CBTsh or TAU - using a web-based randomization service at the Peninsula Clinical Trials Unit which will be concealed from the research team. We will use minimization to ensure balance between arms in relation to site in order to assist with efficient study management (East Dorset, West Dorset, North Cornwall, and South Cornwall) and factors that may affect the outcomes: PHQ-9 score (Moderate: PHQ-9 score 10 to 14; Moderately Severe: PHQ-9 score 15 to 22) and sex (male or female). The minimization algorithm will contain a stochastic element to maintain a degree of unpredictability when allocating. In order to preserve the blinding of research personnel participants will be informed as to which study arm they have been allocated by a researcher not otherwise associated with the study.

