### Outcome measurements

#### Feasibility outcome measurements

The feasibility of participant recruitment will be examined including numbers assessed for eligibility; numbers eligible; reasons for ineligibility; reasons for non-participation and numbers randomized. Additionally comparisons will be made between recruitment settings and recruitment techniques.

The relative levels of diagnosis of depression between treatment arms at post-treatment (four months) will be determined using the CIS-R.

The feasibility and acceptability of data collection processes will be investigated through the number of missing items and follow -up rates relating to the clinical outcome measurements likely to be used in a Phase III trial. Additionally, we will examine levels of attrition through treatment and study drop-out rates.

The range of number, length, and frequency of support sessions required to bring about recovery from depression, defined as a score of ≤9 on the PHQ-9, as per current IAPT guidance
[65] will also be reported.

The acceptability of the treatment will be examined through reasons reported for not attending support sessions, reasons for withdrawal from treatment and acceptability interviews will be conducted at four months post-randomization.

PWP adherence to the protocol will be examined using audio tapes of treatment sessions. Levels of PWP adherence to the protocol will be judged by a member of academic staff involved in delivering PWP training on an accredited PWP training programme. A randomly selected sample of 20% recorded treatment sessions for each PWP in the study will be assessed for levels of adherence.

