### Clinical outcome measurements

A number of clinical outcome measurements have been included to examine the feasibility of the proposed data collection process, estimates of relative levels of diagnosis of depression between arms at post-treatment and the range of number, length, and frequency of support sessions required to bring about recovery from depression. The CIS-R will be used to assess diagnosis of depression and the PHQ-9 will be taken to measure depression severity. Symptoms of anxiety will be measured using the Generalized Anxiety Disorder 7-item Scale (GAD-7)
[66] and levels of functional impairment will be measured using the Work and Social Adjustment Scale (WSAS]
[67]. Stroke survivors’ mobility skill and self-care will be examined with the Barthel Activities of Daily Living Index (BI)
[68]. The measure will be completed by the informal carer on behalf of the stroke survivor. Discrepancies arise between stroke survivor and informal carer assessment of stroke survivor functional ability, with carers rating patients as more disabled
[69]. However, such disagreement has been found to be associated with increased carer burden
[69] and is therefore of interest to collect. Stroke survivors’ level of functional impairment will be measured through the Frenchay Activities Index (FAI)
[70]. The measure will be completed by the informal carer on behalf of the stroke survivor. Due to bias found when using proxy scores on the FAI
[71] results will be interpreted with caution. However the use of proxy measurements on the FAI are considered suitable for research purposes
[72]. Carer burden will be measured using the Caregiver Burden Scale (CBS)
[73]. We will also measure informal carer quality of life using both the Short Form (36) Health Survey (SF-36)
[74]; and the EuroQol-5D (EQ-5D)
[75]. Finally, health and public service use will be collected using an adapted version of the Client Socio-Demographic and Service Receipt Inventory (CSRI)
[76]. The version of the CSRI for use in this study has been adapted from the original CSRI
[76] and a further version developed for informal carers of stroke survivors
[77].

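### The effect-size objective has no matching analysis: clinical outcomes get a mean and SD, with no between-arm effect measure or confidence interval, and that summary does not suit a yes/no CIS-R diagnosis

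*Protocol article*

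**What the plan says.** Four places in the protocol article promise an estimate of effect:

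- The abstract (Methods/Design) lists the "likely intervention effect size" among the outcomes to be measured.
- Study aims and objectives asks for "estimates of the range of effect sizes" to inform a fully powered Phase III trial.
- Feasibility outcome measurements states: "The relative levels of diagnosis of depression between treatment arms at post-treatment (four months) will be determined using the CIS-R".
- Clinical outcome measurements gives, as one reason for including the clinical measures, "estimates of relative levels of diagnosis of depression between arms at post-treatment".

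The Sample size section adds that 30 per arm should indicate how large a later trial would need to be.

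For clinical outcomes, the Quantitative part of Statistical analysis says: "The mean and standard deviation for each outcome measurement will be reported at baseline, four, and six months". The same paragraph attaches 95% confidence intervals to recruitment and attrition rates, and calls the analysis mainly descriptive.

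On the CIS-R, Clinical outcome measurements says: "The CIS-R will be used to assess diagnosis of depression and the PHQ-9 will be taken to measure depression severity". Table 1 lists it with the other outcome measures, at full screen, four months and six months.

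**The concern.** The analysis paragraph sets out what will be reported and which quantities get an interval, yet nothing in it answers the effect-size question. It names no difference in means, standardised difference, risk difference or ratio, and does not say that the means and SDs will be given by arm. Someone following it would have columns of means and would have to derive the effect themselves, without adjustment for baseline or for the factors used in minimisation.

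At stake is the hand-over to Phase III. A point estimate from about 60 people says little unless its uncertainty travels with it, and a designer who sees only means and SDs may treat the apparent difference as far better known than it is.

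The generic sentence also covers the CIS-R, which the protocol uses as a diagnosis, although a diagnosis calls for counts and proportions.

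**Working it through.** **No plan figure to reproduce.** The 30 per arm rests on a cited recommendation. The protocol states no power, alpha, target effect, SD or dropout. The calculations below only show how much uncertainty a bare mean and SD would leave unreported.

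**Promise against analysis**

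| Promised | Where | Matching item in the Quantitative section |
|---|---|---|
| Recruitment and attrition rates | Aims; Feasibility outcome measurements | Rates with 95% CI |
| Likely effect size and its range | Abstract; Aims | None; mean and SD per time point |
| CIS-R diagnosis compared between arms at four months | Feasibility and Clinical outcome measurements | None; falls under the generic mean and SD |

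**Standardised difference**

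Inputs: n = 30 per arm (Sample size section), or 24 per arm if 20% are lost (assumption). Formula: half-width = 1.96 × √(2/n + d²/(4n)).

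- d = 0, n = 30: 1.96 × √(0.0667) = 0.51
- d = 0, n = 24: 1.96 × √(0.0833) = 0.57
- d = 0.5 (assumed observed value), n = 30: 1.96 × √(0.0667 + 0.0021) = 0.51, so the interval is −0.01 to 1.01
- d = 0.5, n = 24: 1.96 × √(0.0833 + 0.0026) = 0.57, so the interval is −0.07 to 1.07

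**What that means for Phase III**

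Assume 90% power and a two-sided 5% level, with n per arm = 2 × (1.96 + 1.28)²/d². An observed 0.5 gives 85 per arm. The upper limit of 1.01 gives 21 per arm. The lower limit of −0.01 gives no useful size at all.

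**CIS-R diagnosis**

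Coded 0/1, the mean is the proportion and the SD follows from it. With 18 of 30 diagnosed, the mean is 0.60 and the SD is √(30 × 0.6 × 0.4/29) = 0.498. With 12 of 30, the mean is 0.40 and the SD is again 0.498. The SD carries no further information. At entry the summary is a constant, because the inclusion criteria require the diagnosis.

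For a risk difference, half-width = 1.96 × √(p₁(1−p₁)/n + p₂(1−p₂)/n). With assumed rates of 40% and 60%:

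- n = 30: 1.96 × √(0.008 + 0.008) = 0.248, interval −45 to +5 percentage points
- n = 24: 1.96 × √(0.010 + 0.010) = 0.277, interval −48 to +8 percentage points

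**Gain from baseline adjustment**

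Adjustment multiplies the half-width by √(1 − r²), where r is the correlation of baseline with follow-up (assumed 0.4 to 0.6). At 24 per arm:

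- r = 0.4: 0.566 × 0.917 = 0.52
- r = 0.6: 0.566 × 0.800 = 0.45

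The cost in degrees of freedom is 1 for the measure's own baseline, 1 for PHQ-9, 1 for sex and 3 for four sites: 6 in all, or 5 when the measure is the PHQ-9 itself.

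**The case against.** The strongest reply has four parts.

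*This is detail for a statistical analysis plan.* The article is condensed, and a fuller plan may hold the estimators. That stands for the choice of covariates and the interval method. It does not dispose of the mismatch: the section states what will be reported and where intervals apply, and omits a stated objective. Calling the analysis mainly descriptive does not settle it either, since a difference with an interval is an estimate and needs no hypothesis test.

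*A between-arm comparison is promised.* This is correct. A reader might infer from the analysis section that no between-arm estimate will be produced and that no outcome or time point is singled out. The documents do not support that: both outcome sections single out CIS-R diagnosis, compared between arms, at four months. What they lack is the effect measure and its interval.

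*Effects can be derived.* If summaries are given by arm, as is usual in a parallel-group trial, the mean, SD and n yield a crude standardised difference and an interval. The output would be incomplete rather than unobtainable. The protocol does not define the range of effect sizes; a confidence interval is the natural reading, but a spread across measures is possible.

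*The CIS-R point is loose drafting.* Partly so. The mean of a 0/1 variable is its proportion, so nothing is biased. The sentence still needs to fit the measure.

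A reader might also infer that the largest of many effects will be carried into Phase III. Nothing in the documents says so, and no weight is put on it here.

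**Conclusion.** The point holds as a mismatch between objective and analysis, of moderate severity. The stated analysis gives clinical outcomes no between-arm effect measure and no interval, although effect size is an objective and a comparison of diagnosis is promised. Mean and SD is unsuitable for that diagnosis.

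The half-width of about 0.51 SD follows from the planned 30 per arm. The figure of 0.57 rests on the assumed 20% loss, and the diagnosis rates, the observed effect of 0.5, the correlations and the Phase III power are also assumptions. None of them is needed for the mismatch itself.

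Randomisation, trial conduct and the primary feasibility results are unaffected, and the data needed are already to be collected. That is why this is not graded higher.

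**What to change.** Amend the Quantitative part of Statistical analysis as follows.

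1. Report all clinical summaries by arm, with participants as randomised.
2. For each continuous measure, report the between-arm difference at four and six months with a 95% confidence interval, adjusted for that measure's baseline value (initial-screen value for PHQ-9 and GAD-7, following Table 1) and for the minimisation factors: PHQ-9, sex and site. Add the standardised difference.
3. Report CIS-R diagnosis as n/N (%) per arm with a risk difference and 95% confidence interval, with four months as the time point already singled out.
4. Name in advance the outcome that supplies the headline effect size for Phase III. If it is not CIS-R diagnosis at four months, say how the two relate.
5. State that these are estimates and that no significance claims will be made.

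The cost is a few sentences, minor analyst time and five to six degrees of freedom in the adjusted models. No new data, visits or participants are needed.

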### Participant inclusion criteria

Eligible participants will be self-identified informal carers of stroke survivors at a minimum of two months post-home discharge (relating to the time of the most recent stroke), aged 16 and over. We will recruit participants meeting the 10th revision of the International Statistical Classification of Diseases and Related Health Problems (ICD-10) criteria for major depression as determined by the Clinical Interview Schedule (CIS-R)
[49] and who score between 10 and 22 on the Patient Health Questionnaire-9 (PHQ-9)
[50]. To reflect standard practice participants will be eligible to participate in the study whether or not they are currently receiving antidepressant medication, however the dose must have been stable for at least one month prior to recruitment into the study. All participants need to be able to read in English in order to engage with the written CBTsh intervention.

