### Treatments

#### Intervention

Participants will receive one assessment session and up to twelve support sessions. Limiting the number of sessions used to support the intervention is identified as one of the characteristics associated with low-intensity CBT
[59]. The number of support sessions received will be decided collaboratively between the PWP and participant. The initial assessment session will be of 35 minutes duration, with subsequent sessions lasting between 25 and 35 minutes each. During their first assessment session participants will receive the CBTsh introduction workbook specifically developed for the trial
[42]. The assessment session will mainly comprise a client-centered assessment to understand the difficulties experienced by the participant alongside the provision of information concerning the impact of depression, the impact of the caring role on mood, and the CBT approach. Participants will also be provided with more information about each of the three possible interventions (behavioral activation, problem solving, and goal setting) by the PWP, supplemented by the introduction workbook
[42]. During the first support session participants will be provided with an additional workbook detailing the particular CBTsh intervention they wish to use (behavioral activation, problem solving, or goal setting). Subsequent support sessions will provide guidance and encouragement around the use of the chosen CBTsh intervention. All assessment and support sessions will follow a structured treatment support protocol
[60] adapted to fit the needs of carers that were identified within the treatment development phase. Assessment and support sessions will be provided either face-to-face, over the phone, or through a combination of both methods as determined by participants’ preference. All participants will receive relapse prevention during their final support session, again guided by a relapse prevention workbook developed for the study.

Those providing support will be qualified PWPs trained in accordance with the curriculum supporting the Improving Access to Psychological Therapies Programme
[61,62] to deliver low-intensity CBT-based interventions for depression and anxiety
[63]. PWPs will also receive an additional one day training session delivered by the first author, alongside a carer of a stroke survivor and a stroke healthcare professional. Consistent with IAPT supervision guidance for the PWP workforce

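### The PHQ-9 schedule shown does not reveal when recovery occurs, so the mean number of sessions needed for recovery is not identified and its bias has no known direction

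*Protocol article*

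**What the plan says.** The outcome appears in three sections of the protocol article, and two further sections govern the data behind it.

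- **Feasibility outcome measurements** plans to report the range of number, length and frequency of sessions "required to bring about recovery from depression, defined as a score of ≤9 on the PHQ-9".
- **Clinical outcome measurements** says the clinical measures were included partly to supply "the range of number, length, and frequency of support sessions required to bring about recovery from depression".
- **Quantitative** (under Statistical analysis) gives a different summary: "The mean and standard deviation will also be reported for the number, length, and frequency of support sessions required to bring about recovery".
- **Data collection, Table 1** gives the PHQ-9 time points as "Initial screen; four months post-randomization; six months post-randomization".
- **Intervention** allows up to twelve support sessions after the assessment session and says: "The number of support sessions received will be decided collaboratively between the PWP and participant".

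Feasibility outcome measurements treats four months as post-treatment. No section says which PHQ-9 reading defines recovery for this outcome, who is in the denominator, or how carers who do not recover are counted.

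**The concern.** A number of sessions needed for recovery is a time-to-event quantity measured in sessions. To know it for one carer, one must see the session at which the PHQ-9 first falls to 9 or below. To summarise it for a group, one must also account for carers who stop, or reach the twelfth session, before that happens. The article describes neither.

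What can be counted on the schedule shown is the number of sessions attended by carers whose PHQ-9 is 9 or below at a later visit. That count reflects when practitioner and carer agreed to finish, because nothing links the end of treatment to the cut-off.

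The Abstract lists this as feasibility outcome (e), and the Discussion says the feasibility questions are to inform a Phase III design. A figure labelled as what recovery requires would be read as a statement about how much support is needed, which these data cannot support.

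**Working it through.** **Step 1: is the quantity observed?** Entry requires a PHQ-9 of 10 to 22, so no carer meets the cut-off at entry. The next listed PHQ-9 is at four months, described as post-treatment. A carer scoring 9 or below then may have crossed after any session, or after the last one. At six months recovery may also have come after the sessions ended. The crossing session is not recoverable from these time points.

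**Step 2: what if the crossing session were known?** The plan gives no figure to reproduce, so this is an illustration. Assumptions, not in the documents: the session of recovery T is geometric with constant chance h per session, and every carer continues to recovery or session twelve. The cap of 12 is from the Intervention section.

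- Proportion recovered by session twelve: R = 1 − (1 − h)^12
- Restricted mean over everyone, non-recoverers counted at 12: E[min(T, 12)] = R / h
- Mean over recoverers only: E[T | T ≤ 12] = (R/h − 12(1 − h)^12) / R

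For h = 0.05: (0.95)^12 = 0.5404, so R = 0.4596. The restricted mean is 0.4596/0.05 = 9.19. The recoverers-only mean is (9.193 − 12 × 0.5404)/0.4596 = 5.89.

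| h | R | Recoverers only | Restricted mean | Shortfall |
|---|---|---|---|---|
| 0.05 | 46% | 5.89 | 9.19 | 3.30 |
| 0.10 | 72% | 5.28 | 7.18 | 1.90 |
| 0.15 | 86% | 4.68 | 5.72 | 1.04 |
| 0.25 | 97% | 3.61 | 3.87 | 0.26 |

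From h = 0.05 to 0.15 the restricted mean falls by 9.19 − 5.72 = 3.47 sessions, the recoverers-only mean by only 5.89 − 4.68 = 1.21. The second is a poor guide to the first.

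**Step 3: what if it is not known, as on the schedule shown?** The recorded count then includes L further sessions attended after the unseen crossing: E[min(T + L, 12) | T ≤ 12]. The smallest L at which this exceeds the restricted mean is:

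| h | L | Recorded mean among recoverers | Restricted mean |
|---|---|---|---|
| 0.05 | 4 | 9.24 | 9.19 |
| 0.10 | 3 | 7.99 | 7.18 |
| 0.15 | 2 | 6.58 | 5.72 |
| 0.25 | 1 | 4.60 | 3.87 |

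Against the uncapped mean 1/h the reversal comes at L = 6 for h = 0.10 (10.17 against 10.0), L = 3 for h = 0.15 (7.48 against 6.67) and L = 1 for h = 0.25 (4.60 against 4.0). It never comes for h = 0.05, where 1/h = 20 lies above the cap. The documents give neither h nor L, so they do not settle the sign.

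**The case against.** The strongest reply is that Table 1 is not a full inventory. Session number and length and the session recordings are collected but absent from it, so its silence does not prove that no PHQ-9 is taken during treatment. Treatment is given in IAPT services, sessions follow a cited structured support protocol, and the full protocol and SAP are not shown. This stands as a caveat. It does not rescue the outcome: the article describes no sessional PHQ-9 and ties the outcome to the scheduled clinical measures. If sessional scores do exist, the recoverers-only mean runs into the shortfall in Step 2.

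It is also fair that averaging over recoverers is nowhere stated, and that a denominator is often left to a SAP. But a carer who never recovers has no observed value of this quantity, so a plain mean and SD has no obvious place for that carer. Early stoppers are not lost from reporting altogether, since drop-out rates with 95% confidence intervals and attendance categories are planned. The analysis is mainly descriptive, with 30 carers per arm.

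Three stronger readings are tempting but unsupported:

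- *The figure will come out too low.* This holds only if the crossing session is recorded. On the listed schedule, later sessions push the other way.
- *Session length is fixed and so uninformative.* The article gives a range, "with subsequent sessions lasting between 25 and 35 minutes each".
- *The recovery cut-off is wrong because it sits one point below the entry floor.* The article attributes the cut-off to IAPT guidance, and the present point does not depend on it.

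**Conclusion.** The point holds in a limited form. On the PHQ-9 schedule shown, the number of sessions needed for recovery is not identified, and the direction of bias in the planned mean is unknown. If sessional scores exist, a mean over recoverers only is biased low, by 3.30 sessions at an assumed 5% recovery chance per session and by 1.04 at 15%. Those sizes rest on a constant chance per session and no drop-out, and serve as illustration only.

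Separately, the article promises a range in two sections and a mean and SD in a third for the same outcome.

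This is more than missing detail, because the article itself fixes the label, the measurement times and the summary. It is still a moderate matter: it affects what can be concluded from one descriptive outcome and leaves the recruitment, attrition and data-collection results untouched. A reader might infer that this mean would set the Phase III dose or cost. No section says so. The article says only that feasibility findings inform the later design and that processes for estimating delivery costs will be tested.

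**What to change.** 1. Rename the outcome *sessions received* and delete the wording about what recovery requires wherever it occurs.
2. Report median, IQR and range of number, length and frequency for everyone randomized to CBTsh, including those who attended none or stopped early, split by PHQ-9 of 9 or less at four months. State the denominator and how a missing four-month PHQ-9 is shown.
3. Align Feasibility outcome measurements and Clinical outcome measurements (range) with Quantitative (mean and SD) on this one set of summaries.
4. If PHQ-9 scores are already recorded at sessions, say so. Then also summarise the session of first PHQ-9 of 9 or less by Kaplan-Meier over all CBTsh carers, censoring at end of treatment or session twelve. Report the cumulative proportion recovered by session with 95% confidence intervals. A median alone is not enough: at an assumed 5% per session only 46% recover by session twelve, so it would not be expected to be reached.

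**Cost.** Items 1 to 3 need wording changes and no new data, which matters because recruitment has begun. The price is a less ambitious label and slightly more analysis. Item 4 assumes that drop-out and early agreed discharge are unrelated to recovery. That is doubtful when the end of treatment is a joint decision, and it should be stated beside the result.
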